### Study outcomes

The primary outcome of the study is to assess the feasibility of implementing a meditation routine in the perioperative period. This will be evaluated using the adherence data from patients’ meditation diary. Secondary exploratory outcomes include effects of the intervention on pain, sleep, psychological wellbeing, cognitive function, and delirium. A number of tools, including pain scores, questionnaires for cognition and delirium assessment, depression and anxiety questionnaire, sleep questionnaires, total opioid consumption and supplemental analgesic requirements in the first 48 h postoperatively, Intensive Care Unit (ICU) stay, and hospital length of stay, will be used to measure the secondary outcomes. In addition, we will also evaluate inflammatory biomarkers measured in plasma. All secondary outcomes will be considered hypothesis generating and interpreted as such (Fig. 2).

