### Neurocognitive and psychological assessments

A trained research team member who remains blinded to treatment allocation will perform baseline cognitive, delirium, anxiety, and depression assessments. Cognitive function will be assessed using the Montreal Cognitive Assessment (MoCA), supplemented with days of the week (DOW) and months of the year (MOY) for additional attention testing. The Delirium Symptom Interview (DSI) will be used to capture delirium. The Depression, Anxiety, and Stress scale (DASS-21) will be used to assess the baseline psychological state. Using data from the cognitive testing and DSI, the researcher will complete the Confusion Assessment Method (CAM), which includes an assessment of delirium using the CAM diagnostic algorithm. If this baseline assessment shows a DASS-21 depression score > 10 or MoCA score < 10, the individual will be excluded from the study.

To assess the changes over time, or the possible effect of perioperative meditation, a telephonic MoCA (t-MOCA) will be administered preoperatively within 24 h before surgery. These assessments will take place before initiation of any sedatives or other medications that may affect the patient’s performance or ability to complete the assessment.

On each postoperative day during the hospital stay, a blinded research team member will administer a standard cognitive assessment, including DOW, MOY, CAM, and the DSI. If an individual is intubated postoperatively, a CAM-ICU will be performed instead of a CAM assessment. If daily assessments have plateaued for three consecutive days and the patient remains CAM-negative each day, assessments will then be completed every other day if the individual remains CAM-negative, until the date of discharge. On the day of discharge, the MoCA, DOW, MOY, CAM, DSI, and the DASS-21 will be completed.

A follow-up assessment will be administered at one month (± seven days) after the date of surgery. These will be completed by a blinded research team member via telephone and will include a T-MoCA, DOW, MOY, CAM, DSI, and DASS-21. Medications that were taken 6 h before the assessments, as reported per the individual, will be documented at all time points.

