### Sleep questionnaires

The Pittsburgh Sleep Quality Index (PSQI), which measures quality and patterns of sleep during the past month, will be completed at baseline and at the one-month follow-up. The PROMIS – Sleep Disturbance and the PROMIS – Sleep Related Impairment questionnaires will be completed weekly from baseline until the day of surgery, preoperatively within 24 h of surgery and weekly after surgery through the one-month follow-up. These questionnaires may be completed in person or via telephone.

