### Statistical analysis

In this feasibility study, a convenience sample of 30 participants (10 per group) will be enrolled to assess feasibility. While we expect it to be very rare, it is possible that some individuals may be determined ineligible after signing consent (because of their baseline MoCA or DASS-21 depression scores). Therefore, we plan to enroll enough patients to obtain data from 30 randomized participants. We estimate that approximately 40 patients may be enrolled to account for dropouts, loss of follow-up, and to achieve this sample size of 30. No a priori power calculation was performed.

Since the primary outcome of the study assesses the overall feasibility of conducting the trial, our descriptive study will record the proportion of patients eligible who meet inclusion without exclusion criteria and decide to participate. The statistics for overall protocol adherence to the intervention will be recorded by reporting the total number of sessions completed out of that required per protocol. We will also assess the total number of questionnaires completed out of the total required.

Descriptive statistics of data will be performed. Categorical data will be reported as proportions and assessed with the use of a chi-square or Fisher’s exact test. Continuous data will be reported as means ± standard deviations or median (quartile 1 and quartile 3) depending on distribution and assessed using analysis of variance (ANOVA). We estimate that with a small sample size it may not be acceptable to assume normality and may be appropriate to use a non-parametric equivalent such as Kruskal–Wallis test when appropriate. A trajectory analysis will be performed to assess changes in the presence of delirium or changes in cognitive function over time. Since the secondary outcomes are exploratory in nature, all tests will be two-sided, with *p* values < 0.05 considered statistically significant. Data will be analyzed using SAS 9.4 (SAS Institute Inc., Cary, NC, USA) or later. Our primary analysis will be conducted using the intention-to-treat principle. All trial reporting will adhere to the Standard Protocol Items: Recommendations for Interventional Trials (SPIRIT; Additional file 1: Table S1).

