### Future direction

A reasonable compliance to the meditation schedule in the intervention groups will denote feasibility and will lay down the foundation for a more elaborate study. Comparison between the two intervention groups will provide an estimate of the optimal timeframe and duration of the intervention necessary to achieve the desirable outcomes. Sensitive, quantitative tools have been used to examine and measure the magnitude of effect for various outcomes such as pain, sleep, delirium, cognitive decline, depression, anxiety, and inflammatory biomarkers. One or more positive outcomes along with their respective effect sizes will inform on the endpoints and sample size of an adequately powered study in the future.

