### Limitations

One potential limitation is the possibility for loss to follow-up. This could significantly impact the study, given the relatively small sample size. A flexible timeframe for the one-month follow-up will help minimize this issue. Further, we have accounted for loss of follow-up and dropouts and have planned to enroll 40 patients in order to achieve a sample size of 30 participants. This study includes only one academic medical center and its patient population. While we are in an urban area, the study population may not be a completely representative sample of those who undergo these types of procedures. Delirium and pain may be transient and it might be difficult to measure them accurately despite the use of sensitive tools. Randomization should help minimize this limitation.

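### Questionnaire completion is fixed as one pooled ratio, which would still read about 77-89% if every one-month form were missed

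*Protocol article*

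**What the plan says.** The Statistical analysis section opens its feasibility paragraph with "Since the primary outcome of the study assesses the overall feasibility of conducting the trial" and then lists participation among eligible patients, meditation sessions completed out of those required, and finally: "We will also assess the total number of questionnaires completed out of the total required". No split by instrument or visit is stated, and no threshold.

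The forms that feed this ratio are set elsewhere in the article:

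- **Inpatient:** "On each postoperative day during the hospital stay, a blinded research team member will administer a standard cognitive assessment, including DOW, MOY, CAM, and the" (the fourth instrument in this list is the DSI). Testing moves to alternate days once results have plateaued for three days in a patient who stays CAM-negative. Six instruments are due at discharge.
- **One month:** "A follow-up assessment will be administered at one month (± seven days) after the date of surgery". This covers T-MoCA, DOW, MOY, CAM, DSI and DASS-21 by telephone, plus the PSQI and a satisfaction survey.
- **Sleep:** the two PROMIS forms "will be completed weekly from baseline until the day of surgery, preoperatively within 24 h of surgery and weekly after surgery through the one-month follow-up". The PSQI is due only at baseline and one month.

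Study outcomes refers to the cognition and delirium tools as questionnaires, so it is natural to count them. The same section says of the primary feasibility outcome: "This will be evaluated using the adherence data from patients’ meditation diary".

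**The concern.** A pooled total weights each form by how often it is scheduled. Baseline, preoperative, inpatient and weekly forms together far outnumber those due at one month, so the one-month assessment carries little weight.

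That is the assessment most at risk. The Limitations section begins: "One potential limitation is the possibility for loss to follow-up". It says this could matter a good deal in so small a study, and relies partly on a flexible one-month window to contain it. The pooled ratio is the only measure of outcome-data completeness that the article states, and it cannot show whether that safeguard worked. A future trial with one-month T-MoCA, DASS-21 or PSQI as an endpoint needs exactly that information. For the PSQI, losing the one-month form removes all change data, because there are only two time points.

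The denominator is also settled after randomisation. It grows with length of stay, which is itself a secondary measure, and shrinks when testing is thinned.

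**Working it through.** The article states no completion rate, so there is no figure to reproduce. The check counts required forms per participant.

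**Inputs from the article**

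- Baseline: MoCA, DOW, MOY, DSI, CAM, DASS-21, PSQI and two PROMIS forms = 9.
- Preoperative: two PROMIS forms at one intermediate week, then t-MoCA and two PROMIS forms within 24 h before surgery = 5.
- Inpatient with daily testing and discharge on day L: 4 × (L − 1) + 6.
- Postoperative weeks 1-3: two PROMIS forms each = 6.
- One month: six telephone instruments, PSQI, two PROMIS forms and the satisfaction survey = 10.

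**Assumptions:** a 14-day lead to surgery (the minimum allowed) and L from 4 to 14 days. Length of stay is not given.

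**Formula:** T = 9 + 5 + [4 × (L − 1) + 6] + 6 + 10. With every one-month form missed and all else complete, the ratio is (T − 10)/T.

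- L = 5: T = 52, ratio 42/52 = 80.8%.
- L = 7: T = 60, ratio 50/60 = 83.3%.
- L = 10: T = 72, ratio 62/72 = 86.1%.

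**Other counting rules.** Thinned testing is taken as days 1-3 and then alternate days, which gives 3 assessment days before a day-4 discharge and 8 before a day-14 discharge. If only CAM and DSI count among the four daily tests, the blocks are 7 baseline, 5 preoperative, 2 per inpatient day plus 4 at discharge, 6 weekly and 8 at one month. If the four tests count as one battery, they are 6, 5, 1 per inpatient day plus 3 at discharge, 6 and 7.

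| Counting rule | 4-day stay | 14-day stay |
|---|---|---|
| Four tests separately, daily | 38/48 = 79.2% | 78/88 = 88.6% |
| Four tests separately, thinned | 38/48 = 79.2% | 58/68 = 85.3% |
| CAM and DSI only, daily | 28/36 = 77.8% | 48/56 = 85.7% |
| CAM and DSI only, thinned | 28/36 = 77.8% | 38/46 = 82.6% |
| One battery, daily | 23/30 = 76.7% | 33/40 = 82.5% |
| One battery, thinned | 23/30 = 76.7% | 28/35 = 80.0% |

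The range is 76.7% to 88.6%. A narrower one-month set of seven forms (PROMIS counted as four separate postoperative weeks, no satisfaction survey) gives higher values: 44/51 = 86.3% at 5 days and 80/87 = 92.0% at 14 days.

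**For the planned 30 participants** with a 5-day stay and daily testing, 30 × 52 = 1560 forms are due. With all 300 one-month forms missing, the pooled ratio is 1260/1560 = 80.8%. By time point, the same data read 100% everywhere except one month, which reads 0/300 = 0%.

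**Effect of length of stay.** Fixed completion rates are applied to stays of 5 and 14 days (inpatient forms 22 of 52 and 58 of 88):

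- Inpatient 90%, one month missed, rest complete: (0.9 × 22 + 20)/52 = 76.5% rises to (0.9 × 58 + 20)/88 = 82.0%.
- Inpatient 60%, all else complete: (0.6 × 22 + 30)/52 = 83.1% falls to (0.6 × 58 + 30)/88 = 73.6%.

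The ratio moves with length of stay at unchanged completion per form, and the direction depends on which forms are missed.

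**The case against.** The strongest reply is that this is a reporting detail. The sentence describes a supporting measure in a condensed article. It has no threshold and does not rule out a table by instrument and visit, which a full protocol or analysis plan may contain. That limits the weight of the point but does not remove it: the article states a numerator and a denominator, and both are pooled.

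Four stronger readings are tempting, and the article does not support them.

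- **That the primary result is compromised.** A reader might infer this from the paragraph in which the sentence sits. But Study outcomes ties the primary outcome to the meditation diary, and Future direction says: "A reasonable compliance to the meditation schedule in the intervention groups will denote feasibility". No decision rule uses questionnaire completion.
- **That inpatient tests dominate the ratio.** With daily testing and each test counted, they are 22/52 = 42.3% of forms at 5 days and reach half only at about 7 days (30/60). With thinning, half is reached at about 10 days (30/60). Counted as one battery, they are 6/30 = 20% at 4 days and 16/40 = 40% at 14. The masking comes from all the other forms together.
- **That longer stays make completion look better.** This holds only if inpatient completion exceeds completion elsewhere. The article gives no such rates, expects that some patients may be intubated, and announces no comparison of completion between arms.
- **That the ratio is blind to any loss after discharge.** If the weekly PROMIS forms for weeks 1-3 were lost as well, and all of them are treated as post-discharge, the ratio would be 32/48 = 66.7% at 4 days and 72/88 = 81.8% at 14 (each test counted, daily testing). It does respond to wider loss; it is weak for the one-month assessment in particular.

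**Conclusion.** The point holds as a modest, inexpensive improvement to a supporting descriptive measure. As defined, the pooled ratio would stay at about 77-89% with no one-month data at all, for assumed stays of 4 to 14 days and under every counting rule in the table. It can therefore conceal the loss to follow-up that the article itself flags. Its denominator depends on length of stay and on the thinning rule, so it can shift either way for reasons unrelated to completion per form. The exact percentages rest on the assumed stay, the 14-day lead and the choice of which forms count. The masking itself does not depend on inpatient forms being a majority. Nothing here affects the diary-based primary outcome.

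**What to change.** In the Statistical analysis section, replace the pooled total as the main completion measure with completion by instrument and time point (baseline, preoperative, inpatient, discharge, weekly PROMIS, one month), by arm. Show one-month completion of T-MoCA, DASS-21 and PSQI separately, out of all randomised participants, so that withdrawals count as not completed. For inpatient tests, first compute each patient's share of due assessments completed, then summarise over patients, so that long stays do not carry extra weight. The pooled total can remain as a supplementary line.

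The cost is a sentence in the plan and one extra table from data already planned for REDCap, with no added visits, staff or participants. The downside is that the headline completion figure will probably look less favourable.

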### Recruitment and randomization

Individuals will be identified from perioperative surgical consult lists and cardiac surgery clinic visit schedules. If a candidate is eligible for enrollment, he or she will be approached by a member of the research team to discuss the study in detail. Written informed consent will be obtained before initiation of any study procedures.

After obtaining consent, enrolled participants will be randomly assigned to one of three groups using block randomization in a 1:1:1 allocation. REDCap will be utilized to implement the randomization schema while maintaining the blind. REDCap is a secure software designed for rapid data capture tools using metadata table referenced by presentation-level operational modules [24]. Patients will be randomized to one of the following groups:Group 1: Patients are asked to meditate twice daily, starting from least two weeks before surgery, up until four weeks after surgery;Group 2: Patients are asked to meditate twice daily from the day after surgery until four weeks after surgery;Group 3: Patients in the control group will undergo surgery and subsequent hospital stay according to the current standard of care, which does not include meditation.

Patients who are actively meditating previously and are willing to participate in the study will be asked to refrain from meditating during the study period if they are randomized to the control group. They will be required to follow the IK meditation schedule during the period of study participation if they are randomized to one of the intervention groups.

The inclusion of a control group will allow for quantification of the natural history of surgery and postoperative complications. Further, we are utilizing two interventional groups to assess whether a prehabilitative strategy results in differences as compared to a mitigation strategy. Two intervention groups will also help us determine the optimal duration of intervention and the possible impact of duration on compliance and other secondary outcomes.

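### Continuous outcomes are assigned a three-group omnibus test with no baseline term or contrast named, which does not yield the Group 1 v Group 2 comparison or the effect sizes the trial wants

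*Protocol article*

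**What the plan says.** **The test.** Under Statistical analysis, continuous data are to be reported as mean and SD or median and quartiles, "depending on distribution and assessed using analysis of variance (ANOVA"). Because normality may fail in a small sample, it "may be appropriate to use a non-parametric equivalent such as Kruskal–Wallis test when appropriate". The section adds that "all tests will be two-sided, with" p below 0.05 counted as significant. It names no covariate, pairwise contrast or interval. One further analysis is named: "A trajectory analysis will be performed to assess changes in the presence of delirium or changes in cognitive function over time".

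**The comparison and product wanted.** Recruitment and randomization gives the reason for two meditation arms: "we are utilizing two interventional groups to assess whether a prehabilitative strategy results in differences as compared to a mitigation strategy". Future direction says: "Comparison between the two intervention groups will provide an estimate of the optimal timeframe and duration". The abstract (Methods) and Future direction both say that effect sizes from this trial will be used to design a later one.

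**The baselines collected.**
- DASS-21: baseline, discharge and one month (Neurocognitive and psychological assessments).
- PSQI: "will be completed at baseline and at the one-month follow-up" (Sleep questionnaires).
- Both PROMIS sleep scales: weekly from baseline, before surgery, then weekly to one month (same section).
- Plasma: baseline, before surgery and postoperative day 2 (Blood collection).
- MoCA: baseline, with telephone or in-person repeats.

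No baseline is described for pain. Opioid use in the first 48 hours, ICU stay and hospital stay are postoperative by nature.

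**Size.** "a convenience sample of 30 participants (10 per group) will be enrolled to assess feasibility", with about 40 enrolled to reach that number and no power calculation.

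**The concern.** The named test and the stated purpose do not match. A 2-df omnibus test asks whether any of three groups differs. It does not estimate how far starting two weeks before surgery differs from starting the day after, which is the stated reason for having two meditation arms. Kruskal–Wallis gives no estimate on the outcome's scale at all. Someone designing the next trial needs a difference, its direction and its uncertainty.

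The second issue is precision. With 10 per arm, chance baseline differences between arms are sizeable. An analysis without the baseline value carries them into the effect sizes used for later planning, although for several outcomes the data to remove them are already being collected. What is at stake is how usable and how precise the secondary estimates are, not the feasibility conclusion.

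**Working it through.** **1. Is there a stated figure to reproduce?** Only the sample size: 3 × 10 = 30, and 30/40 = 0.75, so enrolling 40 implies a 25% loss. The article gives no effect size, SD or baseline–outcome correlation. The figures below are in SD units with 10 analysed per arm, and the correlation r is an assumption shown over a range.

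**2. Does the omnibus test identify which strategy is better?** The F-test's power depends only on λ = n Σ(μᵢ − μ̄)².
- Take illustrative means of (0.8, 0.4, 0) for Groups 1, 2 and 3: λ = 10 × (0.16 + 0 + 0.16) = 3.2, and power is 30.9%.
- Reordered as (0, 0.4, 0.8) or (0.4, 0, 0.8), λ is again 3.2 and power is again 30.9%.

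The test behaves identically whether prehabilitation is the best arm, the worst or in between. This step needs no assumption about correlation.

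**3. How large is chance baseline imbalance?** The difference between two arm means at baseline has SD √(1/10 + 1/10) = √0.20 = 0.45. The chance that it exceeds 0.5 SD in either direction is 2 × [1 − Φ(0.5/0.447)] ≈ 26% for any one pair of arms.

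**4. What does baseline adjustment gain?** Half-width of the 95% CI for one pairwise difference:
- Unadjusted, 27 residual df: t(0.975, 27) × √0.20 = 2.052 × 0.447 = 0.92.
- ANCOVA, 26 residual df: t(0.975, 26) × √[0.20 × (1 − r²) × (1 + 1/25)], where 1/25 is the expected penalty for chance imbalance in the covariate.

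| Assumed r | Fall in residual variance (r²) | Half-width (SD) | Change in width | Equivalent unadjusted n per arm, 10/(1 − r²) |
|---|---|---|---|---|
| 0 | 0% | 0.94 | about 2% wider | 10.0 |
| 0.3 | 9% | 0.89 | about 3% narrower | 11.0 |
| 0.5 | 25% | 0.81 | about 12% narrower | 13.3 |
| 0.7 | 49% | 0.67 | about 27% narrower | 19.6 |

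The last column ignores the lost degree of freedom. A 4,000-run simulation agrees: mean half-width is about 0.91 unadjusted, against 0.93, 0.88, 0.80 and 0.66 adjusted at r = 0, 0.3, 0.5 and 0.7.

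**5. Which outcomes does each part reach?**
- *Unused baseline:* DASS-21, PSQI, PROMIS sleep and plasma biomarkers. Cognition also has the trajectory analysis, which uses repeated measurements. Pain, opioid use and length of stay have no described baseline to use.
- *Missing contrast:* all continuous outcomes. The trajectory analysis does not state its group comparisons either.

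**The case against.** The strongest reply is that this is a condensed article and that an analysis plan may add covariates and contrasts. The text does not say that the ANOVA is unadjusted, and it does not rule out follow-up comparisons. That stands as a limit: a reader might infer that the trial has decided against baseline adjustment, but the article is only silent on it. It does not dispose of the point, because the article does name a test, and that test does not match the comparison stated elsewhere in the same article.

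Other objections also narrow the point:
- A reader might infer that every measured baseline is ignored, MoCA included. The planned trajectory analysis of cognitive function does not support that.
- A reader might infer that all three pairwise estimates are promised. Only Group 1 v Group 2 is named; the control group's stated role is to quantify natural history.
- Group means and SDs will be reported when data are roughly normal, so crude differences could be derived. That is true, but they would be unadjusted, and medians and quartiles do not give them directly.
- The gain depends on an unstated correlation and need not be the same for all outcomes. Excluding patients with psychiatric history or a baseline DASS-21 depression score above 10 restricts that scale's range and would tend to lower its correlation.
- All secondary outcomes are declared hypothesis generating, and even 0.67 SD is a wide half-width for sizing a trial. Both are fair. Where the product is estimates, though, intervals on named contrasts serve it better than an omnibus p-value.

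**Conclusion.** The point holds as a mismatch between the named test and the stated purpose, with a precision gain available on some outcomes. The mismatch applies to all continuous outcomes and rests on the text alone. The unused baseline applies to DASS-21, PSQI, PROMIS sleep and plasma biomarkers, and rests on reading the article's silence on covariates as no adjustment.

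The size of the gain is conditional: from about 3% narrower intervals at r = 0.3 to about 27% at r = 0.7, against about 2% wider at r = 0. It assumes 10 analysed per arm, a common SD and a linear baseline relation. Quoting only the upper part of that range would overstate it.

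The consequence is moderate to minor. It would be wrong to conclude that the feasibility result is in doubt: the primary outcome is descriptive adherence and does not use these tests. The change is still worth making, because effect sizes for the next trial are the stated use of the secondary data.

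**What to change.** Amend the analysis wording as follows.
- **Outcomes with a baseline** (DASS-21, PSQI, biomarkers): fit ANCOVA with the baseline value as covariate. For weekly PROMIS, fit a mixed model with the baseline value as covariate. Handle skewed outcomes by transformation or bootstrap rather than ranks, so that the effect stays on an interpretable scale.
- **All continuous outcomes, including pain, opioid use, ICU stay and hospital stay:** report Group 1 v 2 and each meditation group v control with 95% CIs. Label them exploratory estimates, not further tests at 0.05.
- **Omnibus ANOVA or Kruskal–Wallis:** keep as supportive only.
- **Trajectory analysis:** state which group contrasts it will report.
- **Optional sensitivity analysis for preoperative outcomes:** compare Group 1 with Groups 2 and 3 pooled. The contrast variance is 1/10 + 1/20 = 0.15 against 0.20 for Group 1 v Group 3, an SE ratio of √(0.15/0.20) = 0.87. This is not free: it assumes that Group 2's single supervised practice session at enrolment has no effect.

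The cost is one residual degree of freedom per adjusted model and a few sentences of text. No extra patients, visits or measurements are needed.
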